## Abstract

**Background:**

Geriatric patients are at high risk of re-admission after discharge. Pre-existing nutritional risk amongst these patients is of primary concern, with former nutritional intervention studies being largely ineffective. None of these studies has included individual dietary counselling by a registered dietician or has considered competing medical conditions in the participants. A former randomised study has shown that comprehensive discharge follow-up in geriatric patients homes by general practitioners and district nurses was effective in reducing the re-admission risk in the intervention group compared to the control group. That study did not include a nutritional intervention. The purpose of this study is to assess the combined benefits of an intervention consisting of discharge follow-up in geriatric patients' home by a general practitioner and a registered dietician.

**Methods/design:**

This single-blind randomised controlled study, will recruit 160 hospitalised geriatric medical patients (65+ y) at nutritional risk. Participants will be randomly allocated to receive in their homes, either 12 weeks individualised nutritional counselling by a registered dietician complemented with follow-up by general practitioners or a 12 weeks follow-up by general practitioners alone.

**Discussion:**

This trial is the first of its kind to provide individual nutritional intervention combined with follow-up by general practitioner as an intervention to reduce risk of re-admission after discharge among geriatric medical patients. The results will hopefully help to guide the development of more effective rehabilitation programs following hospital admissions, which may ultimately lead to reduced health care costs, and improvement in mobility, independence and quality of life for geriatric patients at nutritional risk.

**Trial Registration:**

ClinicalTrials.gov 2010 NCT01249716

## Background

Undernutrition is common in old people admitted to the hospital and nutritional state often deteriorates further during hospital stay [1]. Therefore, at discharge a high amount of old patients will still be undernourished or at-nutritional risk: A recent study among 2076 old rehabilitation patients (80.6 y) have found that 85% were at risk of undernutrition (MNA 17-23.5) or undernourished (MNA < 17) according to the Mini Nutritional Assessment (MNA) and that length of stay was higher in those two groups compared with the well-nourished (p < 0.001) by 18.5 and 12.4 days respectively [2]. And an older study among old people (81 y) discharged to their own home has found that those with empty refrigerators were more frequently readmitted and three times sooner than those who did not have empty refrigerators [3].

Potentially the period after discharge is the most important time to intervene, because hospital stays are generally short and getting shorter.

Further, according to the Resolution from the Council of Europe patients in need of nutritional support should receive such treatment before admission (where possible), at the earliest opportunity during hospital stay and after discharge [4].

In spite of this, there is a dearth of published evidence of benefit or harm:

According to our knowledge six studies has assessed the benefits of oral nutritional support to geriatric patients at risk of or already undernourished, initiated in relation to discharge [5-11].

In most studies a positive effect of the intervention was found on the energy and nutrient intake, the nutritional status and in some also the functional status. In contrast the effect on the rehabilitation capacity, the quality of life and the survival was very limited.

One explanation for the limited effect observed could be that the length of the majority of studies was relatively short, 4-8 weeks. This may be a problem since e.g. it can be seen from the data presented by Miller and co-workers [10] that participants in both intervention and control group continues to loose weight, both during the 6 weeks intervention and in the 6 weeks after.

Another explanation for the limited effect could be the high number of re-admissions - especially found in the studies among the medical patients. This may have worsened the outcome for an already very frail population. Inappropriate medical treatment often has inadvertent effects, and a considerable number of admissions are attributable to inappropriate medical treatment that could be avoided. In a former randomised Danish study it was shown that comprehensive discharge follow-up in geriatric patients homes by general practitioners (GPs) and district nurses was reducing the re-admission risk in the intervention group compared to the control group after 12 weeks (29 vs. 39%, p = 0.044) [12]. The main focus in that study was GPs follow-up on hospital treatment, and medications, with no special emphasis on nutrition.

A third explanation for the limited effect could be the relatively low level of compliance with the oral nutritional supplements reported in some of the earlier studies [5,6,9]. None of these studies have included individual goal setting, energy dense menus, and counselling focussing on nutritional risk factors, i.e. the expertise from a registered dietician (RD).

All in all, a comprehensive approach to nutrition support, rather than commercial oral nutritional supplements alone, is likely to be required to improve nutritional status and prevent re-admissions, and hence impact positively on functional outcomes and quality of life.

The purpose of this study is to assess the combined benefits of an intervention consisting of discharge follow-up in geriatric patients' home by a GP and a RD.

## Methods/design

### Design

This study is designed as a randomised controlled trial comparing discharge follow-up in patients' home by GP vs. discharge follow-up in patients' home by GP and RD. Patients are eligible for this study when they are 65+ years old and at nutritional risk according to the level 1 screen in NRS2002 [13].

The primary outcome parameter will be the prevalence of re-admissions in the intervention and control group. Secondary outcomes will be changes in body weight, muscle strength, quality of life, and rehabilitation capacity.

### Feasibility of recruitment and sample size

An earlier study has shown that 50% of the elderly hospital population is at nutritional risk according to the level 1 screen [14]. For a clinically relevant difference of 10% in re-admissions and an expected drop-out rate of 12% (based on [12]), a statistical significant level of 0.05 and a power of 80%, two groups of 80 patients are calculated to be necessary.

A pilot study has shown that inclusion of up to 10 patients at nutritional risk per week is feasible. Taking in account an expected refusal rate of 30% at inclusion and loss to follow-up of 10% during the 12 weeks intervention, we aim to include two groups of 90, to be reached in approximately 6 months.

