Most of the former discharge studies may have had an intervention time that was too short to have a realistic chance of detecting differences in morbidity, functional status or quality of life. According to a recent Cochrane Review future trials need to have sufficient statistical power and length of follow-up to be able to detect any beneficial effects [23]. The follow-up period of 12 weeks is therefore chosen because this seems a reasonable time to achieve benefits of nutritional intervention in older people at nutritional risk. Further, in a former study of discharge follow-up in patients home by GPs, there was seen a significant different in the number of re-admissions after 12 weeks [12].

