### Weaknesses

In the Danish study offering discharge follow-up in patients' home [12] the inclusion criteria were aged 78+ years. This means that the participants in this study will be younger, probably less frail and maybe less susceptible to re-admissions. However in the former nutritional intervention studies among 65+ year old geriatric patients, at risk of or already undernourished, the prevalence of re-admissions has been high - up till 56% [5].

Also, in the Danish study offering discharge follow-up in patients home, district nurses were part of the intervention [12]. Due to structural changes in the involved municipalities this is no longer possible. To try to compensate for this, regularly contact with district nurses will be arranged.

In this study there are possibilities of contamination between intervention and control groups since some GPs may be involved in both groups. Since the aim of the study can not be blinded to the GPs, the chosen method may raise the GPs attention in relation to nutritional aspects in both intervention and control participants.

On the other hand the GPs will be paid by the project for their discharge contacts, since such contacts are not yet obligatory. This fact may bias this study towards a *better *effect than can be obtained in daily practice.

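### 80 patients per group give roughly 22–35% power, not 80%, for a 10-point difference in re-admissions

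*Protocol article*

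**What the plan says.** The primary outcome is the prevalence of re-admissions (Design; Outcome parameters), taken from the national register after 12 weeks. The sample-size section sets the target effect, "For a clinically relevant difference of 10% in re-admissions", allows 12% drop-out, and concludes: "a statistical significant level of 0.05 and a power of 80%, two groups of 80 patients are calculated to be necessary". It then raises the recruitment aim to 90 per group to cover 10% loss to follow-up. It gives no control-group rate and does not say whether the test is one- or two-sided.

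The article cites two sets of re-admission rates. The Background gives the earlier Danish trial of GP and district-nurse follow-up as "29 vs. 39%, p = 0.044". The Weaknesses section says that in earlier nutrition trials "the prevalence of re-admissions has been high - up till 56" per cent.

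**The concern.** A 10-point difference between two proportions in the 30–50% range normally needs several hundred patients per group, so 80 looks too small by a large factor.

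The error bears on the primary comparison in two ways. If the real power is far below 80%, a non-significant result says little about a 10-point benefit, yet the stated power suggests the opposite reading. And if significance requires an observed difference well above 10 points, a significant result will tend to overstate a true 10-point effect. The Discussion says that positive results would justify wide implementation. It also cites a review's call that "future trials need to have sufficient statistical power and length of follow-up to be able to detect any beneficial effects", though it does so mainly to support the 12-week follow-up.

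**Working it through.** **Inputs.** From the sample-size section: difference 10 points, alpha 0.05, power 80%, drop-out 12%, 80 per group (80 × 0.88 ≈ 70 evaluable), recruitment aim 90 per group (90 × 0.90 = 81 evaluable). Assumptions: a two-sided test, and a control rate taken from the rates the article cites. These are 39% (control arm of the Danish trial), 29% (its follow-up arm) and 56% (the highest rate quoted). The 10% is read as percentage points because 39% and 29% differ by 10 points.

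**Formula** (two proportions, pooled variance under the null, equal groups, d = p1 − p2, p̄ = their mean):

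n = [1.96·√(2p̄(1−p̄)) + 0.8416·√(p1(1−p1) + p2(1−p2))]² / d²

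**Trying to reproduce 80.** For 39% vs 29%:

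- √(2 × 0.34 × 0.66) = 0.6699
- √(0.39 × 0.61 + 0.29 × 0.71) = 0.6662
- n = (1.96 × 0.6699 + 0.8416 × 0.6662)² / 0.01 = 351.1, so 352 evaluable
- with drop-out: 352 / 0.88 = 400 per group

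| Control vs intervention | Evaluable per group | After ÷ 0.88 | Ratio to 80 |
|---|---|---|---|
| 29% vs 19% | 286 | 325 | 4.1 |
| 39% vs 29% | 352 | 400 | 5.0 |
| 56% vs 46% | 392 | 446 | 5.6 |

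Variants at 39% vs 29% do not close the gap. A continuity correction gives 371 evaluable and a one-sided test gives 277. Reading 10% as a relative reduction (39% vs 35.1%) gives about 2,400. Even 20% vs 10% needs 199. A figure of 70 to 80 evaluable appears only with a control rate of about 10% (two-sided) or 11–12% (one-sided), which nothing in the article supports.

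**Power at the planned size.** Power = Φ{[d√n − 1.96·√(2p̄(1−p̄))] / √(p1(1−p1) + p2(1−p2))}. For 39% vs 29% with n = 80: (0.1 × 8.944 − 1.3130) / 0.6662 = −0.628, and Φ(−0.628) = 0.265.

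| Two-sided power | n = 70 | n = 80 | n = 90 |
|---|---|---|---|
| 29% vs 19% | 28% | 31% | 35% |
| 39% vs 29% | 24% | 26.5% | 29% |
| 56% vs 46% | 22% | 24% | 27% |

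A simulation of 400,000 trials at 39% vs 29% gives 23.9%, 26.9% and 29.6%. The 81 evaluable patients left from 90 give 26.8%.

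**Detectable difference at 80% power**, from a 39% control rate: about 21 points (n = 70), 20 (n = 80), 19 (n = 90). From 29%: about 19, 18 and 17 points.

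**What a result would look like.** With n = 80 and rates near 39% and 29%, significance needs an observed difference of about 1.96 × √(2 × 0.34 × 0.66 / 80) = 14.7 points, and the 95% confidence interval has a half-width of about 14.6 points. If the trial observed exactly 39% vs 29%, z = 0.10 / 0.0749 = 1.34 and p ≈ 0.18. In the simulation, the significant results at n = 80 showed a mean difference of about 19 points although the true difference was 10.

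**Cross-check from the cited trial.** Its p = 0.044 for the same 10 points implies about (2.014)² × 2 × 0.34 × 0.66 / 0.01 ≈ 182 per group, assuming equal groups and an uncorrected chi-square test. A trial more than twice this size only just crossed 0.05 when it observed the full 10 points.

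**The case against.** The best objection is that no single power figure can be called the actual one, because the section states neither a control rate nor sidedness. That is correct. The 24–27% figure belongs to 39% vs 29%, two-sided, with 70 to 80 evaluable. It can also be argued that 39% is the wrong anchor. Both groups here receive GP follow-up, so the earlier trial's follow-up arm (29%) may be the nearer control rate, and the article expects a younger and perhaps less susceptible population. Against that, district nurses are no longer part of the intervention and rates up to 56% are cited, so the uncertainty runs both ways.

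Seventy evaluable may also be too pessimistic. Re-admissions come from a register and the analysis is by intention to treat, so a patient who leaves the home visits need not be lost to the primary outcome, and the aim is 90 per group.

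These points widen the range but do not rescue the claim. The most favourable case among the cited rates (29% control, all 90 evaluable) gives 35% two-sided and 47% one-sided.

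Two further points stand. The Statistical analysis section already plans 95% confidence intervals for differences in percentages, so that part of the remedy only needs tying to the primary outcome. And the article states no rule for interpreting a null result, so misreading one is a risk created by the stated power, not something the plan prescribes.

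**Conclusion.** The stated sample size is wrong. At the re-admission rates the article cites, a 10-point difference needs about 286 to 392 evaluable patients per group. After drop-out that is about four to five and a half times the stated 80. Two-sided power with 70 to 90 per group is 22% to 35%, and about 24% to 29% at 39% vs 29%. The exact figure depends on the assumed control rate, a two-sided test and the number evaluable. The conclusion that power is far below 80% does not: one-sided testing, the larger recruitment target and complete follow-up leave it below 50%, and a relative reading of 10% makes it worse. This must be corrected, since it misstates what the primary comparison can show.

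**What to change.** Replace the power statement in the sample-size section with figures that name their assumptions, for example: *With 80 (90) patients per group, a two-sided 5% level and a control re-admission risk of 39%, the trial has about 27% (29%) power for a 10-point difference, and 80% power only for a difference of about 20 (19) points. With a control risk of 29%, power for 10 points is about 31% (35%).*

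State that the primary result is the risk difference with the 95% confidence interval already planned, and that a non-significant result will not be read as absence of a 10-point benefit.

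The cost is a change of wording and a less favourable stated power; no extra patients are needed. The change corrects the claim but leaves the trial small. Keeping 80% power for 10 points would take about 400 per group at 39% vs 29%. At the planned pace (180 patients in about 6 months), 800 patients would take about 800 / 180 × 6 ≈ 27 months.

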#### Re-admissions (t = 12)

A register-based evaluation of readmissions will be done after 12 weeks. Data on admission to the hospital will be based on the National Patient Register. Information about the number of days to first re-admission and the number of days spent in hospital will also be collected from the Register.

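### The article gives two enrolment totals (160 and 180) and two attrition rates (12% and 10%), and does not say whether 80 per group means enrolled or evaluable

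*Protocol article*

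**What the plan says.** Three statements in the protocol article bear on the number of patients.

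- **Abstract, Methods/design:** the trial "will recruit 160 hospitalised geriatric medical patients (65+ y) at nutritional risk".
- **Feasibility of recruitment and sample size, first paragraph:** the inputs are a 10% difference in re-admissions, 12% drop-out taken from the former Danish discharge study, a 0.05 significance level and 80% power. From these, "two groups of 80 patients are calculated to be necessary".
- **Same section, second paragraph:** a pilot showed that "inclusion of up to 10 patients at nutritional risk per week is feasible". The authors then allow for "an expected refusal rate of 30% at inclusion" and for "loss to follow-up of 10% during the 12 weeks intervention, we aim to include two groups of 90", to be reached in about six months.

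Two further sections show whom attrition affects. Under Re-admissions (t = 12), the primary outcome is register-based: "Data on admission to the hospital will be based on the National Patient Register". Under Statistical analysis, the primary analysis follows intention to treat.

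**The concern.** The number to be randomised is a figure on which the trial's budget, timetable and final report all rest. Here a reader can cite one sentence for 160 and another for 180. The expected loss over the same 12 weeks is 12% in one paragraph and 10% in the next, and nothing relates the two.

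As written, 80 per group already allows for drop-out, yet the second paragraph adds an allowance for loss and arrives at 90. Either the allowance was made twice, or one of the sentences describes 80 wrongly. A later report that compares achieved with planned recruitment would have no single plan to compare with.

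**Working it through.** **Inputs.** From the abstract: 160. From the sample-size section: 80 per group, 12% drop-out, 90 per group, 10% loss, 30% refusal, up to 10 patients a week, about six months.

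**Step 1: totals.** 2 × 80 = 160, so the abstract and the first paragraph agree. 2 × 90 = 180, so the second paragraph does not. Difference: 20 patients; 20/160 = 12.5%.

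**Step 2: where 90 comes from.** Enrolled = evaluable/(1 − loss).
- At 10%: 80/0.90 = 88.9, so 89, close to 90.
- At 12%: 80/0.88 = 90.9, so 91, also close to 90.

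Either rate takes 80 to roughly 90. Refusal does not explain the step: it happens before inclusion, so it lengthens accrual without changing the number included.

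**Step 3: try each reading.**

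| Reading of 80 | Consequence | What then fails |
|---|---|---|
| Enrolled, 12% already included | 80 × 0.88 = 70.4 evaluable per group; enrol 160 | The aim of 90 per group |
| Evaluable | Enrol 89 per group (178) at 10%, or 91 (182) at 12% | The abstract's 160, and 12% as an input to the 80 |
| 12% and 10% are separate, successive losses | 90 × 0.90 × 0.88 = 71.3 evaluable per group; enrol 180 | The abstract's 160; the article does not describe two stages of loss |

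Each reading leaves at least one statement wrong.

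**Step 4: accrual.** Applying refusal to the pilot rate gives 10 × 0.70 = 7 a week.
- 180/7 = 25.7 weeks, or 25.7 × 12/52 = 5.9 months.
- 160/7 = 22.9 weeks, or 5.3 months.

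The stated six months fits 180 better. This is supporting evidence only, because the pilot rate is an upper figure.

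**Step 5: does either total give 80% power?** The sample-size section gives no control rate. I assume the 39% and 29% that the Background cites from the former Danish study, an absolute difference, equal groups and a two-sided 0.05 test with pooled variance under the null.

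Mean rate = 0.34. Null term: 1.960 × √(2 × 0.34 × 0.66) = 1.960 × 0.6699 = 1.313. Alternative SD: √(0.39 × 0.61 + 0.29 × 0.71) = √0.4438 = 0.6662.

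- Required n = [(1.313 + 0.842 × 0.6662)/0.10]² ≈ 351.1, so 352 per group before any drop-out. The plan's 80 is not reproduced.
- Power = Φ[(0.10 × √n − 1.313)/0.6662].
  - n = 80: Φ(−0.628) = 26.5%
  - n = 90: Φ(−0.547) = 29.2%

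Other control rates do not rescue it. For 29% versus 19% the requirement is 286 per group, and for 56% versus 46% (56% being the highest re-admission rate cited, under Weaknesses) it is 392. A two-sided requirement of 80 per group needs a control rate near 10.4%, well below the 29% to 56% cited.

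**The case against.** The strongest defence is that the sample-size section distinguishes a number required (80) from a number to include (90), and that the accrual figures fit 180. On that view the working target is clear and the abstract merely quotes the required number. Much of this stands: 160 and 80 per group are one target, so the article holds two totals, not three, and the section read alone does give an aim of 90 per group. A reader might infer that the end of enrolment is undefined. The text does not support that; it supports two conflicting totals.

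It can also be said that drop-out and loss to follow-up are different terms and might refer to different stages, since consent may be given in hospital and randomisation follows discharge. That is possible, so double counting is the natural reading but not a certain one. It does not rescue the abstract's figure, and the article defines neither term.

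Two stronger inferences are tempting, and neither is supported.

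- **Recruitment could be stopped at whichever total suits**, because staff know the allocation. Knowing allocation is not knowing comparative outcomes. No interim look is described, re-admissions are evaluated from the register after 12 weeks, and the principal investigator is to be re-blinded before analysis.
- **The wording invites a completers-only primary analysis.** The article specifies intention to treat and a register outcome, which point the other way.

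Nor can one say that attrition is irrelevant to the primary outcome. The article does not say how withdrawal of consent or death before 12 weeks affects register data, so some loss there cannot be excluded.

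**Conclusion.** The inconsistency is real and can be checked from the text: 160 against 180 to be enrolled, 12% against 10% attrition, and an 80 per group that is not identified as enrolled or evaluable. The discrepancy is 20 patients. That 90 is 80 inflated again for loss is an inference from 80/0.90 = 88.9. If it is right, the effect is more patients, not fewer, so no power is lost through it. No bias is demonstrated. The point should be corrected because it concerns a core design figure and the correction is cheap.

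A reader might also infer that settling on 180 would put the sample size in order. It would not. Moving from 80 to 90 per group takes power only from 26.5% to 29.2% under the assumptions in the working (39% versus 29%, absolute difference, two-sided, equal groups). The gap to the stated 80% is a separate and larger fault, which reconciling the totals leaves untouched.

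**What to change.** 1. State one number to be randomised, in the same words in the abstract and in the sample-size section. The article's accrual figures (7 a week over about six months) correspond to 180. If the sponsor keeps that total, it should be given as the enrolment aim and not presented as adequate for 80% power.
2. Say whether 80 per group is enrolled or evaluable, and apply one attrition rate once. If 12% and 10% are meant as different losses, define each and the stage at which it occurs.
3. State that randomised patients are analysed for re-admission by intention to treat through the National Patient Register, so that attrition mainly concerns the outcomes measured at home at 12 weeks.
4. Correct the power statement separately, giving the assumed control rate, whether the 10% difference is absolute, and whether the test is two-sided.

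Items 1 to 3 cost only wording. Item 4 may not: it requires either a larger trial or an open statement of what 160 or 180 patients can detect.
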